## Description of protocol

### Study design

This study will adopt a prospective, parallel randomized controlled trial design and aligns with the Standard Protocol Items: Recommendations for Interventional Trials (SPIRIT) checklist. Participants will be required to provide written and verbal consent prior to involvement. Once enrolled into the study, participants will complete an online survey to ascertain demographic information, current treatment, management strategies, fertility and loss, perceptions of exercise, current exercise behaviours and preferences, and scores of depression, stress, anxiety, pain, sleep quality, and quality of life. Participants will then complete an initial telehealth consultation which will involve the assessment of functional capacity variables. Furthermore, measures of CRP, estradiol, and cortisol will be analyzed via a dried blood spot sample.

Participants will be provided with an activity monitor (Garmin Vivosmart 5) for activity tracking and monitoring of adherence, and a dried blood spot collection kit. Symptoms and engagement in exercise will be tracked weekly and following the completion of the intervention. Following the completion of the intervention, participants will complete a final telehealth appointment with the research team for assessment of functional capacity variables. Following the completion of the intervention (6 weeks after), participants will be invited to participate in a short (approximately 20 min) one-on-one semi-structured interview to ascertain their lived experience during and following the intervention (Table 1).

**Table 1 tbl0001:** Participant timeline: Schedule of enrolment, interventions, and assessments.

Adapted from Chan et al. [24],.

### Patient and public involvement

The study intervention was informed by a consumer advisory group (CAG) conducted on the 14th of November 2025. The CAG included four women living with endometriosis (one providing written feedback in lieu of meeting attendance) and two accredited exercise physiologists who specialise in exercise management for endometriosis. The CAG provided feedback on the practicality of the intervention, the delivery of the intervention and provided symptom-based advice regarding the intensity and modality of the exercise prescription.

### Participants

Women (*n* *=* 50, assigned female at birth; AFAB; >18y) with medically diagnosed (imaging/ laparoscopy) endometriosis will be invited to participate. Recruitment will occur via various media outlets and will be ongoing in nature. Participants residing in the Australian Modified Monash Model (MMM) areas of MMM2-MMM7 will be invited to participate in the study. Participants must not be pregnant, breast-feeding or undergoing fertility treatment. Further, participants must not have had pelvic surgery, or an intrauterine device inserted or removed for the 6 months prior to beginning the study, and they must not have a diagnosis of adenomyosis. Moreover, participants who fail the 4-stage static balance test, are completing greater than 60 min of exercise per week or are currently using prescription steroids (prednisone or any derivative) will be excluded from the study.

### Pre-assessment and screening

Telehealth consultation (via Zoom) will include an overview of the study, instructions for blood spot sample, activity monitor, and the completion of basic functional capacity assessments. Participants will be screened for any medical condition that may exclude the individual from participating. Abdominal strength will be assessed via a plank duration hold, lower limb strength will be assessed via a wall sit endurance hold test, and global upper limb strength will be assessed by a handgrip dynamometer test, and balance will be assessed via a 4-stage balance test.

## Primary outcome measures

### Activity data

All participants will be provided with a Garmin Vivosmart5 activity monitor for remote activity tracking and adherence logging. Data regarding heart rate, exercise duration and modality will be collected weekly as part of the study. All participants, including passive controls, will be asked to document any incidental exercise completed outside of the study requirements using the Garmin Vivosmart5 activity monitor. The intensity of the walking and yoga sessions will be determined via obtaining the relative percentage of the average HR against age predicted MHR. Furthermore, internal training loads (TRIMP) will be calculated through: Training load = D x (Δ HR ratio) x 0.86e^1.67(Δ HR ratio)^. Moreover, MET-Minutes will be calculated as a secondary unit to measure exercise load.

### Survey data

Demographic information, current exercise behaviours (APSS), scores of depression, anxiety and stress (DASS-21), health-related quality of life (EHP-30), sleep (PSQI), self-efficacy (SEE) and open-ended questions regarding treatment, geographical location, fertility and access to care, will be collected pre- and post-intervention. Moreover, symptoms will be tracked weekly via the Endometriosis Impact Scale (EIS) through REDCap, a survey administration software program.

## Secondary outcome measures

### Biomarkers

Concentrations of estradiol, cortisol and CRP will be assessed via dried blood spot techniques and will be analyzed by Stratech Scientific (APAC, PTY, LTD), according to manufacturer’s instructions.

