## Abstract

Exercise may be an effective tool to improve symptoms and quality of life in those with endometriosis. However, the optimal dose to elicit such changes is unknown. This study will explore the critical threshold of exercise dose required to elicit symptomatic and biomarker changes in women with endometriosis, particularly for those who may be disadvantaged through spatial and aspatial factors.

Fifty women with clinically confirmed endometriosis will be randomly allocated into one of four groups: a passive control, active control (yoga), short duration walking and yoga, long duration walking and yoga.

Participants in the three active groups will complete 12 weeks of exercise.

Symptom severity (chronic) and biomarkers will be assessed pre-post intervention; adherence, and symptom impact (acute) will be assessed each week.

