## Data analysis

All data will be de-identified for analysis and reporting. The estimated sample size was determined using data from Gonçalves et al.[25] where the mean difference for pain between the control and intervention was 24.74, for an effect size of d = 1.33 and comparisons between four groups, a sample size of 32 was estimated (alpha at 0.05 and power 0.80). Factoring in attrition and funding availability, the target sample size was set to 50. However, a piecewise (segmented) mixed-effect regression will be used to determine the critical threshold for exercise dose (primary outcome). Exercise dose (all randomized participants) will be determined by duration and intensity (heart rate) variables, aggregated weekly. For a sample of 50 participants across 12 weeks, with a mixed-effects piecewise model, there will be a minimum of 600 observations, which provide sufficient power and stability for this type of analysis[26]. Threshold and detectable change in slope will be determined by Y^t^ = B^0^ + B^1^* time^t^ + b^2^ * intervention^t^ + b^3^ time after intervention^t^ + e^t^, and confirmed with Davies Test. Intercurrent events such as medication changes, clinical exacerbations and poor adherence will be time- and date-stamped for consideration as co-variates in the regression analysis.

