All other data will be reported as mean ± standard deviation (SD) or median interquartile ranges. Normal distribution will be determined by Shapiro-Wilk’s test and non-normally distributed data will be logarithmically transformed prior to analysis. Pain, as a subset of the EHP-30 is the primary endpoint and will be analysed with an intention-to-treat analysis. A sensitivity (per-protocol analysis) will also be conducted to confirm outcomes. Secondary and exploratory endpoints will be arranged hierarchically as follows; quality of life (EHP-30), depression, stress, anxiety (DASS-21), functional capacity, sleep (PSQI), estradiol, CRP, cortisol. Multiple comparisons will be adjusted for using the Benjamini-Hochberg false discovery rate procedure. Missing data will be managed depending upon the volume of data, complete case analysis will be performed (<5%) for 5–40%, multiple imputation for chained equations or random forest imputation will be employed. Complier average causal effect (CACE) analysis will be employed if compliance varies significantly. Significance will be set at p < 0.05. All statistical procedures will be performed using Statistical Package for the Social Sciences (SPSS; Windows version 31.0, Chicago, IL, USA) and R Studio (2026.07.1).

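### The estradiol comparison pools women with suppressed or postmenopausal estradiol with the rest and takes no account of hormonal status, so the effect is diluted and a null could be misread

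*Protocol article*

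**What the plan says.** **Endpoint.** The protocol article, under Biomarkers, states that "Concentrations of estradiol, cortisol and CRP will be assessed via dried blood spot techniques". The Abstract fixes two time points: "Symptom severity (chronic) and biomarkers will be assessed pre-post intervention". The Data analysis section places the biomarkers at the end of its ordered list of secondary and exploratory endpoints: "functional capacity, sleep (PSQI), estradiol, CRP, cortisol".

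**Who may enter.** The Participants section sets a lower age limit only ("assigned female at birth; AFAB; >18y"). The reproductive exclusions are these: "Participants must not be pregnant, breast-feeding or undergoing fertility treatment". Recent pelvic surgery, recent insertion or removal of an intrauterine device, and adenomyosis also exclude. The one named drug exclusion is for women who "are currently using prescription steroids (prednisone or any derivative) will be excluded from the study"; its parenthesis points to the prednisone class, not to sex hormones. Nothing excludes menopause or stable hormonal treatment. The Background calls drug treatment one of the two most common forms of management, without saying how much of it is hormonal.

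**Allocation.** The Exercise intervention section specifies simple randomisation and names no stratification factor.

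**Use of treatment data.** At entry, "participants will complete an online survey to ascertain demographic information, current treatment, management strategies". The Survey data section adds open-ended treatment questions before and after the intervention. The one stated analytic use is: "Intercurrent events such as medication changes, clinical exacerbations and poor adherence will be time- and date-stamped for consideration as co-variates in the regression analysis". For the remaining endpoints the Data analysis section gives log transformation of non-normal data, false-discovery-rate adjustment and missing-data rules, but no term for hormonal status.

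**The concern.** Where a drug or menopause largely sets circulating estradiol, a 12-week exercise programme has little room to move it. Such women contribute little to the mean change whichever arm they are in. The planned comparison averages them with women whose estradiol can vary, so it estimates a smaller quantity than the effect in the latter group.

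The provision for medication changes does not reach this problem. It concerns changes, whereas stable treatment and menopause are states present at baseline. It also stands in the text on the weekly threshold regression, not in the text on pre-post endpoints. Log transformation does not separate the two kinds of women either.

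What is at stake is interpretation. Biomarker change is in the trial's title and aim, and a null result for estradiol could be reported as exercise not altering it when the cause was the mix of women enrolled. If the responsive subgroup is chosen only after the results are known, it will carry little weight.

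**Working it through.** **The plan's own figure.** The documents give no effect size or power for estradiol. The only sample-size figure concerns pain: d = 1.33, four groups, alpha 0.05, power 0.80, N = 32. It reproduces as a one-way ANOVA with f = 1.33/2 = 0.665 (total 28.9, hence 8 per arm and 32) or as a one-sided t-test (7.77, hence 8 per arm). It is not disputed here and says nothing about estradiol.

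**Inputs.**
- Target 50 in four arms: 50/4 = 12.5, taken as n = 12 per arm (Data analysis).
- q, the share of women on suppressive hormonal treatment or postmenopausal: not documented; assumed 0.3, 0.5 and 0.7.
- Mean effect in those women: assumed near zero, because there is little room to change.
- Delta and sigma: between-arm effect and SD of change in the other women. Both cancel below.

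**Step 1, dilution.** All-women mean effect = (1 - q) x Delta + q x 0 = (1 - q) x Delta.
- q = 0.3: 0.70 Delta
- q = 0.5: 0.50 Delta
- q = 0.7: 0.30 Delta

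If these women respond at a fraction r of the others' effect, the multiplier is (1 - q) + q x r, and the dilution is milder.

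**Step 2, test statistic with equal noise in both kinds of women.**
- All women: (1 - q) Delta / [sigma x sqrt(2/n)].
- Other women only: Delta / [sigma x sqrt(2/((1 - q)n))].
- Ratio, second to first: sqrt(1 - q)/(1 - q) = 1/sqrt(1 - q).

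This gives 1/sqrt(0.7) = 1.20, 1/sqrt(0.5) = 1.41 and 1/sqrt(0.3) = 1.83.

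**Step 3, test statistic if the suppressed women add no noise.** The variance of change over all women is then about (1 - q) x sigma^2, ignoring the small spread between the two group means. The all-women statistic becomes (1 - q) Delta / [sigma x sqrt(2(1 - q)/n)] = Delta x sqrt((1 - q)n/2)/sigma. This equals the statistic in the other women alone. The ratio is 1 and power is unchanged, but the estimate is still diluted as in Step 1.

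**Step 4, size of the responsive subgroup.** 12 x 0.7 = 8.4, 12 x 0.5 = 6 and 12 x 0.3 = 3.6, so about 8, 6 or 4 women per arm before attrition.

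**Step 5, balance.** With Binomial(12, q) in each arm, two given arms differ by 3 or more such women with probability 0.26, 0.31 and 0.26 at q = 0.3, 0.5 and 0.7.

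**The case against.** **Silence in a condensed article.** Covariates for a low-ranked secondary endpoint are often left to the analysis plan, and the article names no covariate for any pre-post endpoint. This stands in part. Handling of values below the assay limit is properly left there and is not raised. But mixed eligibility and unstratified allocation are fixed in this document, and its stated analysis passes over the resulting mixture.

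**Outside physiology.** A reader might infer that these women cannot respond at all. The documents do not say so; they mention neither ovarian suppression nor menopause. Only the weaker premise of little room to change is used.

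**Dilution is not bias.** This stands. The all-women mean is a valid randomised effect for the women enrolled. The trouble begins only when it is read as the answer to whether exercise alters estradiol.

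**Power.** A reader might infer a large, certain loss of power. The factors 1.20 to 1.83 need equal noise, and near-constant low values point towards less. The Limitations section also notes that sampling is not aligned with the cycle, which adds variance among cycling women. Putting the pain effect of 1.33 into an estradiol power calculation has no support in the documents.

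**Imbalance and medication changes.** A reader might infer that chance imbalance (Step 5) produces a false positive. If the suppressed women do not change, their number does not shift the mean change when exercise has no effect. Likewise, treatment started or stopped between samples mimics an exercise effect only if it differs between arms; otherwise it adds noise.

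**Existing caution.** The Limitations section urges care with the biomarkers, but for cycle timing only. It does not cover suppression or menopause.

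**Conclusion.** The point holds as a weakness in how the estradiol endpoint is to be analysed and read, not as an error that invalidates it. The protocol admits women on hormonal treatment and postmenopausal women, does not balance them by design, and states no analysis that takes their hormonal status into account.

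The all-women effect would be about 70%, 50% or 30% of the effect in the other women at assumed shares of 30%, 50% or 70%. The power consequence lies between none and a test statistic smaller by 1.20, 1.41 or 1.83. These figures rest on an undocumented share and on an effect near zero in the suppressed women; the upper factors also rest on equal noise. The direction holds for any share above zero, provided those women respond less than the others.

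The point is worth correcting before outcome data are seen. The primary pain endpoint is untouched.

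**What to change.** In the Data analysis section, in the text on secondary and exploratory endpoints, add for estradiol:

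- an analysis adjusted for baseline estradiol and baseline hormonal status (hormonal treatment or postmenopausal, versus neither), with the all-randomised estimate kept and reported;
- a pre-specified estimate in untreated premenopausal women, named as the one used to judge whether exercise alters estradiol;
- a sensitivity analysis addressing women whose hormonal treatment changed between the two samples.

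**Cost.** No change to eligibility, intervention or visits is needed. Current treatment is already collected and medication changes are already date-stamped. Some of the treatment questions are open-ended, so a short rule for coding answers as hormonal or not should be written in advance. Menopausal status is not among the items named, and age does not establish it; it needs one added item in the existing survey.

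**Downside.** At the assumed shares the subgroup has about 4 to 8 women per arm before attrition, still sampled at random cycle phase. Its interval will be wide, and the report should treat a null there as inconclusive unless the interval excludes effects of interest.

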## Exercise intervention

This study will involve a remote 12- week exercise intervention for regional, rural and remote Australian women living with endometriosis. Participants will be randomly allocated into one of four groups: passive control, active control, shorter duration, longer duration. Allocation will be determined by simple randomization using a randomization table created by computer software (REDCap), with the sequence accessible to one member of the research team only (KB). Central randomization will be utilized for allocation. The passive control will involve usual care, and the active control group will complete 10 min of yoga, three times per week for the 12 weeks (supplementary file 1). The shorter and longer duration exercise groups will complete 10 min of yoga, three times per week in addition to a walking intervention. The shorter duration group will commence at 60 min per week (3 × 20-minute sessions), and the longer duration group will commence at 120 min per week (3 × 40-minute sessions). After six weeks, the total duration in each walking group will be increased to 90 min and 150 min, respectively, with each group increasing session duration by 10 min. Participants will be encouraged to walk as fast as comfortably possible for 1 min, every 5 min of each session.

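### Simple randomisation of 50 women to four arms is valid but leaves arm sizes to chance; permuted blocks would hold them at 11 to 14 for almost no cost

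*Protocol article*

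**What the plan says.** Under Exercise intervention the protocol article states "Participants will be randomly allocated into one of four groups: passive control, active control, shorter duration, longer duration". The method is explicit: "Allocation will be determined by simple randomization using a randomization table created by computer software (REDCap"). One team member can see the sequence, and "Central randomization will be utilized for allocation". The article names no blocking, stratification, minimisation or cap on arm size, and gives no allocation ratio.

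Under Data analysis, the sample size uses d = 1.33 for pain and comparisons between four groups, from which "a sample size of 32 was estimated" at alpha 0.05 and power 0.80. Then: "Factoring in attrition and funding availability, the target sample size was set to 50". Neither a per-arm number nor an attrition rate is given.

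**The concern.** Simple randomisation balances arms well in large trials. With about 12 women per arm, chance imbalance is large relative to the arm. Two things are at stake.

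- **Between-arm comparisons of EHP-30 pain.** An arm that is small by chance weakens every comparison that uses it, and the planned total leaves little slack.
- **Loss after randomisation.** An arm that starts small has less to lose. The Limitations section itself expects that adherence may be low and that attrition may reduce power.

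A short arm cannot be repaired once recruitment closes. This is a method that the article fixes, not a detail left to a fuller document.

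**Working it through.** **Inputs.** From the article: 50 randomised, four arms, simple randomisation, calculated total 32, d = 1.33, alpha 0.05, power 0.80. Assumed: allocation 1:1:1:1, two-sided tests with no multiplicity adjustment, and all 50 randomised.

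**The plan's own figure.** A one-sided two-sample t-test at d = 1.33 needs 7.77, so 8 per arm, and 4 × 8 = 32. A four-group ANOVA with f = d/2 = 0.665 needs 29, which rounds up to 8 per arm, again 32. A two-sided t-test needs 9.93, so 10 per arm, 40 in all. The figure of 32 is therefore reproducible as 8 per equal arm.

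**Arm sizes under simple randomisation.** The four counts are multinomial(50; ¼, ¼, ¼, ¼). One arm has mean 50 × 0.25 = 12.5 and SD √(50 × 0.25 × 0.75) = 3.06, with a central 95% range of 7 to 19. Exact enumeration gives:

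- expected smallest arm 9.0, expected largest 16.2;
- P(smallest ≤ 8) = 35%; P(smallest ≤ 7) = 18%;
- P(largest at least twice the smallest) = 37%;
- P(all four arms 12 or 13) = 1.6%.

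**Power.** For arms n1 and n2, the noncentrality is d√(n1·n2/(n1+n2)) on n1+n2−2 degrees of freedom. Two-sided power at 0.05:

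| Arms | Power |
|---|---|
| 13 v 13 | 0.902 |
| 12 v 13 | 0.889 |
| 12 v 12 | 0.875 |
| 8 v 12 | 0.787 |
| 7 v 12 | 0.750 |
| 8 v 8 | 0.697 |

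Averaged over the multinomial, a prespecified pair has power 0.866. The two smallest arms, the weakest of the six pairs, average 0.794 and fall below 0.80 in 46% of sequences. With arms of 12 or 13 the weakest pair has 0.875.

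**After attrition.** No rate is stated, so four are assumed; 36% is the most that still leaves 32, since 1 − 32/50 = 0.36. Each woman is retained independently. P(some arm retains 5 or fewer):

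| Loss | Simple | Arms of 12/12/13/13 |
|---|---|---|
| 10% | 8% | <0.1% |
| 20% | 19% | 1% |
| 30% | 40% | 11% |
| 36% | 57% | 27% |

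**Arm sizes with blocks, cut at 50.** Blocks of 4 give 12 full blocks (48) plus two women, so always 12 or 13. With blocks of 4 and 8 chosen at random, imbalance beyond that arises in two ways:

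- A block of 8 starts after woman 48 and its first two places go to the same arm (largest arm 14).
- A block of 8 starts after woman 44 and its two unused places belong to the same arm (smallest arm 11).

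A block ends at a given multiple of 4 with probability about 2/3. The next block is an 8 with probability 1/2, and the two places match with probability 1/7. Each route therefore has probability about 2/3 × 1/2 × 1/7 = 1/21. So P(12 or 13 throughout) ≈ 1 − 2/21 = 90.5%, and otherwise the arms are 11 to 13 or 12 to 14. Simulation agrees (0.906).

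**The case against.** The strongest reply is that nothing here is an error. Simple randomisation is unbiased, it is clearly described with central allocation, and it is the least predictable method in an open trial. For one prespecified pair it costs about 1 to 4 points of power on average. All of that stands, and it limits the point to efficiency and the risk of a very small arm. The power figures also depend on two-sided testing, which the article does not state. On the one-sided basis that reproduces 32, power is 0.811 for 8 v 8 and 0.876 for 8 v 12.

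Four stronger readings are tempting but not supported:

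- **A small arm leaves part of the dose axis nearly empty.** In the threshold model, dose is measured weekly from duration and heart rate in all randomised women. Passive controls also log incidental exercise (Activity data), and walking time rises after six weeks. An arm of 9 women could still supply 9 × 12 = 108 weekly observations. With no dropout, some arm has 5 or fewer women in only about 3% of sequences.
- **The plan expects 36% attrition.** It does not. The target of 50 also reflects funding, and 36% is only the largest loss that leaves 32. At that loss some arm falls below 8 in about 85% of sequences even with arms of 12/12/13/13, so attrition is then the main driver. Completer counts also overstate the harm where the planned intention-to-treat analysis imputes missing values.
- **The sample size is stated as 8 per arm.** Equal arms is a reasonable inference from 32 and four groups, but the article gives no per-arm number.
- **Runs of one arm over calendar time will bias results.** Recruitment is ongoing and such runs are possible, but the article shows no calendar trend in pain for them to confound.

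**Conclusion.** The point holds as a cheap improvement, not as a flaw in validity. The chance of a short arm is material: 35% for 8 or fewer and 18% for fewer than 8 at the start. The average power cost is small, and the real cost falls on the comparisons that involve the smallest arms. The advantage of blocking holds across the whole attrition range, although its size varies widely with the rate. The arm-size figures rest on equal allocation and all 50 being randomised. The power figures rest also on d = 1.33, two-sided 0.05 without multiplicity adjustment, and no dropout.

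**What to change.** Under Exercise intervention, replace simple randomisation with equal allocation to the four groups in permuted blocks of randomly varying size (4 and 8), loaded as the same REDCap table. Block sizes should be known only to the team member who holds the sequence. State the 1:1:1:1 ratio in the same sentence.

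The cost is regenerating the list before the first randomisation. If allocation has begun, the new list applies to the remaining women, and the change and its date are reported; the 11 to 14 range then holds only for a list blocked from the start. No extra participants, visits or measurements are needed.

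The downside is slight predictability at block ends in an open trial. Central allocation and undisclosed, varying block sizes limit it. Fixed blocks of 4 would guarantee 12 or 13 but are more predictable, so the mixed sizes are the better compromise.

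### The dose-threshold model pools unmasked usual-care women with the three programme arms, so a shared benefit of having any programme can appear as a low-dose threshold even if dose has no effect

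*Protocol article*

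**What the plan says.** All references are to the Protocol article.

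- **Target.** Under Data analysis, "a piecewise (segmented) mixed-effect regression will be used to determine the critical threshold for exercise dose (primary outcome").
- **Who is in the model.** The same section states: "Exercise dose (all randomized participants) will be determined by duration and intensity (heart rate) variables, aggregated weekly". It counts at least 600 observations from 50 women over 12 weeks.
- **Arms.** Under Exercise intervention, "The passive control will involve usual care". Yoga alone is the second comparison arm: "the active control group will complete 10 min of yoga, three times per week for the 12 weeks". Two further arms add walking to the same yoga, starting at 60 and 120 min per week. "After six weeks, the total duration in each walking group will be increased to 90 min and 150 min, respectively".
- **Weekly outcome.** Under Survey data, "symptoms will be tracked weekly via the Endometriosis Impact Scale (EIS) through REDCap". The other questionnaires are collected only before and after the intervention.
- **Incidental exercise.** Activity data asks every arm, usual care included, to log exercise done outside the study. Participants excludes only women already doing more than 60 min per week.
- **Model terms.** The printed equation contains time, intervention and time after intervention. It has no dose term, and the coding of the intervention term is not given. The candidate covariates are medication changes, exacerbations and poor adherence.

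**The concern.** A woman on usual care cannot be masked to having no programme, and the weekly symptom score is her own report. Usual-care women will mostly supply the lowest doses, and women given a programme will mostly supply the rest. Any benefit of being given a programme that is the same in all three programme arms is then a step near the bottom of the dose axis. A continuous segmented curve in dose can represent such a step only as a rise followed by a bend. The planned Davies test asks whether the slope changes and says nothing about why. The trial could therefore confirm a critical dose when it has only shown that having a programme differs from not having one. The article presents itself as guidance for health and exercise professionals, so such a result could be put to use.

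**Working it through.** **1. Which women the plan counts.** 50 women × 12 weeks = 600, which matches the stated figure. Three of four arms alone would give on average 50 × 3/4 × 12 = 450. The usual-care arm is therefore in the threshold model.

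**2. Prescribed weekly minutes (Exercise intervention).**

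| Arm | Weeks 1-6 | Weeks 7-12 |
|---|---|---|
| Usual care | 0 | 0 |
| Yoga | 3 × 10 = 30 | 30 |
| Shorter walking | 30 + 60 = 90 | 30 + 90 = 120 |
| Longer walking | 30 + 120 = 150 | 30 + 150 = 180 |

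**3. What a pure programme effect looks like without noise.** Let the mean benefit be 0 without a programme and 1 with one, at any dose. Fit mean = a + b₁D + b₂(D − k)₊, where D is weekly minutes and k the knot. For any k from just above 0 to 30, take a = 0, b₁ = 1/k and b₂ = −1/k. The fit at D = 0 is 0. At every D ≥ k it is D/k − (D − k)/k = 1. The fit is exact although dose has no effect. Beyond 30 the fit worsens: over the six prescribed dose levels, equally weighted, the residual sum of squares is 0.007 at k = 35, 0.055 at 45 and 0.154 at 60. With ideal adherence the false knot is therefore at or below the yoga dose, and the data cannot place it within that range.

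**4. How often a bend would be declared.** I simulated 50 women with 12 weekly scores, no dose effect, and a shared benefit in the three programme arms. The model was a random-intercept broken stick in minutes, tested by the largest slope-change statistic over knots, with 5% critical values simulated under no effect.

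The documents do not give the following, so they are assumptions: a shared benefit of 0.3-1.0 SD, intraclass correlation 0.5, near-equal arms, complete data, and the adherence and incidental-exercise settings below.

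| Setting | 0.3 SD | 0.5 SD | 1.0 SD |
|---|---|---|---|
| Full adherence, no incidental exercise | 12% | 27% | 87% |
| About 80% adherence, incidental 0-20 min/week | 8% | 18% | 62% |
| About 80% adherence, incidental 0-60 min/week | 6% | 9% | 26% |
| Range over all variants run | 6-14% | 9-31% | 24-87% |

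**5. Where the false knot falls.** At 1.0 SD with full adherence, 59% of knots were at or below 30 min/week, 35% between 30 and 60, and 6% above 60. With about 80% adherence and incidental exercise of 0-60 min/week, the median was about 80 and 63% were above 60.

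**6. With programme receipt separated from dose.** Adding a programme yes/no term gave false-bend rates of about 1-7% over all settings. Dropping the usual-care arm gave about 4-5% in the main runs.

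**The case against.** **The printed model may already deal with this.** The equation has an intervention term. If it coded programme yes or no, it would be close to the remedy proposed here. That coding is not stated, however, and the equation has no dose term, so it does not describe the dose-threshold model in the surrounding text. The concern rests on that text.

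**The arms overlap.** Usual-care women may do and log up to 60 min per week of their own exercise, and the Limitations section expects that adherence may be low. Overlap weakens the confounding. This objection stands, and it is why the lower rates in the table exist: at 0.3 SD with incidental exercise up to 60 min/week the excess is negligible. A reader might infer that every woman at 30 min per week or more was given a programme; the documents do not support that.

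**Some attention is shared.** Usual-care women also receive the monitor and the weekly survey, and are not exempted from the telehealth contacts. This may reduce a non-specific difference but does not remove the expectation that comes with a programme.

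**Outcome and dose scale are inferred.** The article does not name the outcome of the segmented model. The weekly scale is inferred because no other symptom score can supply 12 values per woman. Dose also includes heart-rate intensity, so knots in minutes do not carry over directly.

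**A no-exercise anchor is legitimate, and covariates may be settled in the analysis plan.** Both points are fair. They argue for keeping the all-arm fit and adding a companion. They do not remove the problem, because the article itself fixes who enters the model and lists its candidate covariates without programme receipt.

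**Conclusion.** The concern holds as a limit on interpretation. As described, the threshold model cannot tell a dose effect from the effect of having a programme, and it can declare a bend when dose does nothing. The inflation above the nominal 5% ranges from negligible to severe. It depends on a non-specific effect whose size the documents do not give and on how much exercise usual-care women log; the largest rates need a shared benefit near 1 SD.

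A reader might go further and conclude that the trial would publish a critical dose just above the yoga prescription. That does not follow. With ideal adherence the false knot is at or below the yoga dose, and with incidental exercise it moves higher and is poorly located. Nor does it follow that the all-arm model is wrong in itself or that any threshold found would be false.

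The separate intention-to-treat analysis of EHP-30 pain does not rely on this dose curve.

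**What to change.** Keep the all-arm threshold model and prespecify a companion fit beside it, either with a programme yes/no term or restricted to the three programme arms. State the coding of the intervention term and name the model's outcome. Describe a threshold as a dose effect only if it is also seen in the companion fit. Otherwise report it as not separable from the effect of having a programme.

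The cost is one covariate or one extra fit, with no change to conduct. The companion fit is less precise. It cannot locate a threshold below the yoga dose, and the programme term also absorbs any true benefit of the yoga. For these reasons it should qualify the all-arm result and not replace it.
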